### Power and sample size calculations

Data obtained from a random sample of black participants recruited from the MetSO Cohort Study has provided a current estimate of the rate of comprehensive assessment of sleep apnea to be expected in the proposed study. Analysis of the data suggested that 47% of participants referred for sleep assessment would adhere to physician recommendations after exposure to TTI, whereas 35% of those in a control group agreed to undergo a sleep assessment. Thus, this represents the likely rate of adherence expected in our AC group. We propose to achieve an adherence rate of 47% among participants exposed to the TTI.

With an expected 12% increase in the adherence rate associated with the TTI, a standard error of 0.10%, and a sample size of 340, the study will be adequately powered (90%) to detect significant increase in the outcome measures using chi-square tests. The primary study outcome in this project is documented receipt of a sleep apnea assessment. A two-tailed test, with alpha = 0.05, comparing adherence rates of 35% with 47% requires 170 participants per group [42]. The precision estimated in that analysis is the approximate expected precision of study data. Specifically, a difference of 12% would be observed at chi-square = 21.03 with a 95.0% confidence interval of 3% to 20%. With the proposed sample size, the study will have 85% power to achieve a one-standard deviation increase in the odds ratio of adherence attributable to proposed mediators: sleep apnea knowledge, self-efficacy, readiness, and trust/rapport with the HE (expressed as continuous variables).

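### The stated precision (standard error 0.10%, chi-square 21.03, 95% CI 3% to 20%) does not follow from 35% versus 47% with 170 per arm, and the three figures contradict each other

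*Protocol article*

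**What the plan says.** All the relevant statements are in the protocol article under Power and sample size calculations.

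- Control rate: "35% of those in a control group agreed to undergo a sleep assessment".
- Intervention rate: "We propose to achieve an adherence rate of 47% among participants exposed to the TTI".
- Test and size: "A two-tailed test, with alpha = 0.05, comparing adherence rates of 35% with 47% requires 170 participants per group". Design and methods confirms 340 in total and 170 in each arm.
- Standard error: "With an expected 12% increase in the adherence rate associated with the TTI, a standard error of 0.10%, and a sample size of 340". From this the section concludes that "the study will be adequately powered (90%) to detect significant increase in the outcome measures using chi-square tests", with power given as 90%.
- Precision: "The precision estimated in that analysis is the approximate expected precision of study data". It then adds that "a difference of 12% would be observed at chi-square = 21.03 with a 95.0% confidence interval of 3% to 20" per cent.

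The same section names documented receipt of a sleep apnea assessment as the primary outcome, so these figures describe what the trial can show on its main endpoint.

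**The concern.** Two proportions near 40%, each based on 170 people, cannot be compared with a standard error of a tenth of a percentage point. A chi-square of 21 is also far too large for a 12-point difference at this size. In addition, on one degree of freedom the difference, its standard error, the chi-square and the confidence interval are tied together, so any one of the last three nearly fixes the other two. The printed values do not fit together.

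At stake is how a reader judges the design. A chi-square of 21.03 corresponds to p of about 0.000005, which suggests that the planned effect would be beyond doubt. If the planned effect in fact gives a p-value only moderately below 0.05, the paragraph conceals a thin margin on the primary outcome.

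**Working it through.** **Inputs**, all from Power and sample size calculations: p1 = 0.35, p2 = 0.47, difference d = 0.12, n = 170 per arm, two-sided alpha 0.05, chi-square test. The pooled rate is (0.35 + 0.47)/2 = 0.41.

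**1. Values that follow from the inputs**

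- Unpooled standard error: sqrt((0.35×0.65 + 0.47×0.53)/170) = sqrt(0.4766/170) = 0.0529, or 5.3 points.
- Pooled standard error: sqrt(2×0.41×0.59/170) = 0.0533, or 5.3 points.
- Pearson chi-square: 0.12²/(2×0.41×0.59/170) = 5.06, p = 0.024. The unpooled version gives 5.14.
- 95% CI: 0.12 ± 1.96×0.0529 = 0.016 to 0.224. Newcombe's method gives 1.5% to 22.1%.
- Smallest observed difference reaching p < 0.05: 1.96×0.0533 = 0.105, or about 10.5 points.

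**2. Attempts to reproduce the printed figures**

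| Variant | Chi-square | Interval |
|---|---|---|
| Printed | 21.03 | 3% to 20% (as 95%) |
| 170 per arm, as planned | 5.06 | 1.6% to 22.4% |
| Whole-number counts near 35% and 47% | 4.4 to 5.4 | 0.8% to 22.7% (widest limits) |
| Same counts, Yates correction | 3.9 to 4.9 | – |
| Log odds ratio, Wald | 5.03 | – |
| 340 per arm | 10.1 | 4.7% to 19.3% |
| 170 per arm, 90% interval | – | 3.3% to 20.7% |
| One sample of 340 against a fixed 35% | 21.5 or 19.7 | – |

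The one-sample test comes near 21.03 without matching it, and it is not the planned two-group test. The 90% interval comes near the printed interval. No variant gives the full set.

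**3. What each printed figure implies for a 12-point difference**

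| Printed figure | Implied standard error | Implied chi-square | Implied 95% CI | Implied n per arm |
|---|---|---|---|---|
| Standard error 0.10% | 0.1 points | (0.12/0.001)² = 14,400 | 11.8% to 12.2% | 476,600 |
| Chi-square 21.03 | 0.12/sqrt(21.03) = 2.6 points | 21.03 | 6.9% to 17.1% | 21.03×2×0.41×0.59/0.12² = 707 |
| 95% CI 3% to 20% | 0.085/1.96 = 4.3 points | 7.0 (d = 11.5 points) to 7.7 (d = 12 points) | 3% to 20% | 0.4766/0.0434² = 253 |
| Planned design | 5.3 points | 5.06 | 1.6% to 22.4% | 170 |

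Allowing for rounding of the printed limits, the third row's chi-square lies between about 6.3 and 8.6. That is still well away from both 21.03 and 5.06.

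**The case against.** Five objections deserve an answer.

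- **The figures may belong to the pilot or a cited analysis.** The text carries that precision over to this study explicitly, and the figures conflict with each other at any single sample size. This does not rescue them.
- **The section never says what the 0.10% is a standard error of.** This is fair. If it means the difference between arms, as printed, it is too small by a factor of about 53 (5.3/0.10). If the percent sign is a slip and 0.10 was meant as a proportion, it is too large: it would give a chi-square of (0.12/0.10)² = 1.44 and an interval of −7.6% to 31.6%. The size and direction of the error therefore depend on the reading, but the figure is wrong under both.
- **The interval may be a 90% interval with the wrong label.** This is plausible. With 80/170 versus 60/170 the difference is 11.8 points with a standard error of 5.3 points, and 11.8 ± 1.645×5.3 is about 3.0% to 20.5%. If so, the interval does come from 170 per arm, but the stated 95.0% is wrong, and the chi-square and standard error remain unexplained.
- **An interval centred on 11.5% rather than 12% can be rounding.** Agreed. The off-centre midpoint is weak evidence and the conclusion does not need it.
- **The figures are illustrative and drive no test or decision rule.** This is also true, and it limits the severity. The interval itself is only moderately too narrow (half-width 8.5 against 10.4 points). The chi-square is the misleading figure.

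**Conclusion.** The concern holds. With the plan's own rates and 170 per arm, the standard error of the difference is 5.3 points, the chi-square for an observed 12-point difference is 5.06 (p = 0.024), and the 95% CI is 1.6% to 22.4%. All three printed figures are wrong for this design. They also imply three incompatible standard errors (0.1, 2.6 and about 4.3 points), so no single change of sample size would reconcile them. The chi-square is overstated by 21.03/5.06, about 4.2 times.

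The result assumes two independent groups of 170 with complete outcome data and an observed difference exactly as planned. The choice between pooled and unpooled variance, or between Wald and Newcombe intervals, changes only the last digit.

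This is a definite error in the justification for the primary outcome and should be corrected, but it does not alter the planned test. The 90% power claim beside it is a separate error: power at 170 per arm is Φ((0.12 − 1.96×0.0533)/0.0529), about 61%, and 90% needs 351 per arm. Correcting that claim would not by itself repair the precision figures.

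**What to change.** In Power and sample size calculations, delete the 0.10% standard error and replace the precision sentence with one such as: *With 170 participants per arm the standard error of the difference is about 5.3 percentage points; an observed difference of 47% versus 35% would give a chi-square of 5.06 (p = 0.024) and a 95% confidence interval of about 1.6% to 22.4%.* It would help to add that an observed difference below about 10.5 points would not reach two-sided significance.

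Revise the 90% power claim, and the statement that 170 per group suffices for it, in the same edit. Otherwise the corrected chi-square of 5.06 would stand next to a power of 90%, which needs an expected value of about (1.96 + 1.28)² = 10.5.

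For the precision figures the cost is wording only: no procedure, data collection or analysis changes. The stated precision becomes less favourable. Trial status reports 311 participants already randomized, so the corrected figures mainly serve the interpretation of the results.

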### Qualitative analysis

For the qualitative analysis, focus groups will be recorded and transcribed verbatim. Field notes from the HE will also be collected and reviewed. Transcripts will be reviewed line-by-line and assigned codes or labels. Similar codes will be grouped into higher order concepts and then categories. Similar categories will be clustered to form overarching themes. These themes will be the major headings describing barriers to adherence with appointment keeping and using CPAP. A detailed codebook of the analytic process will be maintained. Two independently trained RAs will review the transcripts and serve as corroborators. Data analysis will be aided by (Nvivo) software [43,44].

## Discussion

The intervention is designed to be practical so that, if efficacy is demonstrated, it can be widely disseminated. The intervention relies on one-to-one personal contact, a proven method to effect behavioral change, particularly in populations with low levels of literacy and trust. We expect to demonstrate that TTI is feasible in terms of time and cost.

The significance of the intervention lies in its ability to address a public health need in a high-risk population and minimize health disparities, to evaluate an intervention that can reduce sleep apnea-related morbidity in the community, and to improve understanding about how such interventions can be effectively implemented in other settings.

## Trial status

The MetSO trial began in January 2010. To date a total of 311 participants have been randomized to receive either TTI or usual care.

## Abbreviations

AC: attention control; BP: blood pressure; CPAP: continuous positive airway pressure; CVD: cardiovascular disease; DM: diabetes mellitus; FPG: fasting plasma glucose; HE: health educator; HTN: hypertension; MetSO: Metabolic Syndrome Outcome Cohort Study; PI: principal investigator; RA: research assistant; TTI: tailored telephone intervention; WC: waist circumference.
